## Abstract

**Background:**

N95 respirators are used to limit the transmission of respiratory viruses in clinical settings. There are two to three major types of N95 available for all healthcare workers in Hong Kong. However, after the coronavirus outbreak and the consequent shortage of many commonly used respirators, several new N95 respirators were adopted temporarily in clinical settings without evaluation. Prior literature indicates that traditional N95 respirators used in hospitals in Hong Kong are not fit for Chinese people and have fit rates ranging from 50 to 60%. This study aims to investigate and compare the fit rate, real-time leakage, and mask usability of traditional and new N95 respirators among Chinese healthcare workers.

**Methods:**

This study will employ two sequential phases. Phase 1 has a cross-sectional exploratory design used to investigate the fit rate and mask usability of three types of respirators. Phase 2 will examine the effectiveness of respiratory protection by comparing traditional and new N95 respirators by a randomized crossover trial. Eligible participants will be randomly allocated through a controlled crossover experiment to either a traditional or new respirator group (*n* = 100 in each arm) for performing standard clinical procedures. The primary outcome (real-time leakage) will be recorded at 30 s intervals during nasopharyngeal suctioning and cardiopulmonary resuscitation. The secondary outcomes are the fit rate and mask usability. After a 2 min suctioning (15 s twice) and 4 min one-person CPR, the fit rate (assessed by standard N95 fit testing) and mask usability (measured by self-reported mask usability scale) will be recorded as data of post-procedure. After 10 min rest, measurement of real-time leakage (i.e., crossover), fit test, and usability will be repeated.

**Discussion:**

The result of real-time leakage will be a vital indicator of the respiratory protection of Chinese healthcare workers while performing prevalent clinical procedures, such as resuscitation. The fit rate and usability result will serve as an essential reference for consumable purchase policy in clinical settings.

**Trial registration:** ISRCTN registry: ISRCTN40115047. Retrospectively registered on May 9, 2023. https://www.isrctn.com/ISRCTN40115047.

## Introduction

1

### Background and rationale

1.1

Worldwide outbreaks of different infectious diseases have caused an increased awareness of occupational protection among healthcare workers (HCWs). Therefore, the use of N95 respirators as an effective nonpharmaceutical measure to limit the spread of diseases in hospitals is recommended by the World Health Organization (WHO) and the Centre for Disease Control and Prevention (CDC) (1, 2). However, regardless of the shape and brand of such respirators, they are all generally tight-fitting half-facepiece type, and their credibility depends on fit to the wearer (3–5). For ill-fitting respirators, the average penetration by ambient aerosol was found to be 33% compared with 4% for well-fitting respirators (6). To achieve creditable occupational protection, most known authorities, such as the National Institute for Occupational Safety and Health (NIOSH), CDC, WHO, and the Hospital Authority (HA) in Hong Kong, made fit testing compulsory for wearers prior to the use of an N95 respirator (1, 3–5, 7).

N95 respirators are used to limit the transmission of respiratory viruses in clinical settings. Hospitals under the HA and private hospitals regularly provide two to three major types of N95 respirators available for all HCWs, particularly for high-risk caring procedures, such as suctioning, working in airborne precaution rooms, and resuscitation (7). Commonly used types of N95 respirators are the cup-shaped 3 M 1860 (regular or small size), cup-shaped 3 M 8210 (one size), and the three-panel designed 3 M 1870+ (one size) (8–10). Although manufacturers claimed that all traditional 3 M respirators are 86–100% fit for people (8–10), their performance when donned for Chinese people is suboptimal in terms of protection (reflected by fit rate and real-time leakage) and comfort (reflected by mask usability) compared with that of Western people (3–5, 7, 11, 12).

After the coronavirus (COVID-19) outbreak and the consequent shortage of many commonly used respirators, several new N95 respirators, such as Alpha Pro Tech N95 and NASK M0011 Professional Edition, were adopted temporarily in clinical settings without comprehensive evaluation (13, 14). NASK M0011 comprises nanofibers and has an ear-loop design with two plastic clips, which differs from the traditional melt-blown nonwoven material and head-loop design. The nanomaterial features ultra-thin, lightweight, and breathable properties, allowing wearers to use it for the whole day comfortably. Tests through respected international laboratories, such as the Nelson Laboratories, confirmed a virus filtration efficiency of >99.9%. The material for and design of NASK was officially adopted in public hospitals on 24 April 2020 (13, 14). However, given such a considerable effect on infection control and prevention, the evaluation of reasonable fit rate, real-time leakage, and usability was not comprehensively checked. Besides, the CDC warned that donning a respirator with ear loops as the head harness is difficult to achieve an adequate fit (2).

Quantitative fit testing is a recognized method to determine whether a tight-fitting respirator fits a wearer. This method adopts an electronic device to measure the ratio of particular air particles inside and outside the breathing zone (when donned with a respirator), and the ratio (i.e., fit factor) reflects the degree of leakage (3–5). Therefore, fit rate (the overall passing rate of fit testing) would be the primary concern to determine the fit of an N95 respirator to a population. Studies on American and Canadian HCWs indicated that several brands and types of respirators developed in the West (e.g., 3 M 1870 and 1860) fit 90–100% (9, 10). However, local retrospective analysis reported the fit rate of two N95 respirators (i.e., 3 M 1860S and 9210) from 84 to 91 nursing staff working in intensive care units (12). The fit rate was as low as 55–69% only. Further local studies examined the fit rate of several commonly used N95 respirators among nursing students and reported a consistently low fit rate of 57.4–65.0% (3, 4). In contrast to the results of studies conducted in the West, the fit rates of respirators were lower when donned by Chinese people. These results may reveal that tight-fitting N95 respirators require a match between mask design and facial anthropometry of a given population (e.g., face length and width) (15). However, the fit rates of all newly adopted N95 respirators for Chinese HCWs are unclear, except for some of the preliminary findings indicating that locally developed respirators (i.e., NASK head-loop model) provide a better-fit rate (78.8%) after nursing procedures (11).

Most of the pre-set quantitative fit testing systems require the wearer with a donned N95 respirator to perform a series of exercises, including a static portion without body movement and a dynamic portion with normal breathing and designated movement (i.e., side-to-side, and up-and-down head movement, talking or reading a standard set of passages, grimacing, and bending over). These exercises stimulate common working activities in the clinical environment (5, 7, 9). Several local studies have challenged the reliability of real-time protection of respirators during nursing procedures based on the sole result of fit testing because performing specific procedures involved a greater range of body movement, such as changing napkin, suctioning, and nasogastric tube insertion (11, 16, 17). Real-time leakage (also named face-seal leakage) was measured by a validated portable aerosol spectrometer (17). It was found that the different particles concentration (size >0.3 μm, >0.4 μm, >1.0 μm, and > 4.0 μm) inside a fit respirator significantly increased before and during suctioning and nasogastric tube insertion (15). Preliminary results suggested that the fit factor of the NASK head-loop model decreased to less than that of the traditional model (11). However, these studies did not consider testing the real-time leakage of a given “fit” respirator under heaviest-duty processes, such as CPR, which is a life-saving clinical procedure, and compulsory use of N95 respirators in hospital settings (18).

Although HCWs assume some level of personal occupational risk when caring for contagious patients, numerous policies and regulations call for respiratory protection in the healthcare environment, noncompliance is unfortunately quite common (19). In general, mask usability is a concept used to reflect conditions, including discomfort, interference with occupational duties, and poor communication experienced by the wearers of N95 respirators (20). Discomfort is often associated with tight-fitting N95 respirator models, including 3 M models used in Hong Kong. Such discomfort encompasses various sensations and experiences, including facial pressure, facial heat, facial pain, labored movement of facial muscles, or skin itchiness (21, 22). Moreover, poor communication has been a concern with existing N95 respirators, as they diminish speech intelligibility in noisy clinical environments (23). During the COVID-19 outbreak, usability can also reflect the maximum duration for the extended use of a given respirator. This parameter is crucial during the pandemic because of the global shortage of personal protective equipment (24). Poor mask usability influences the compliance of N95 respirator use (19) and reduces the applicability for extended use, as some HCWs do not wear N95 respirators as indicated when performing resuscitation during the non-pandemic period.

Literature indicates that traditional N95 respirators used in hospitals in Hong Kong are not fit for Chinese people, having fit rates ranging from 50 to 65% compared with those among Western people (10, 11). Such a result poses a risk of real-time leakage during caring procedures, including suctioning, nasogastric tube insertion, and resuscitation. Our preliminary results found that real-time leakage happens during care procedures requiring moderate body movement, referring to moderate intensity of physical activity. However, the degree of real-time leakage of traditional N95 respirators during procedures requiring high body movement (e.g., CPR) remains unknown. Additionally, changes in fit factors during and after various caring procedures are also unknown. More importantly, new respirators with nanomaterials and ear-loop with clip designs have been introduced in public hospitals. Nevertheless, the fit rate, real-time leakage, and mask usability of such design have not been evaluated, which poses a threat of uncertainty to HCWs. Therefore, this study aims to investigate and compare the fit rate, real-time leakage, and mask usability of traditional and new N95 respirators among Chinese healthcare workers.

## Objectives

2

### Study objectives

2.1

This study aims to investigate and compare fit rate, real-time leakage, and mask usability of the traditional and new N95 respirators among Chinese healthcare workers.

#### Primary objective

2.1.1

To compare real-time leakage by using traditional and N95 respirators during two clinical procedures, which are nasopharyngeal suctioning and CPR.

#### Secondary objective

2.1.2

To investigate the fit rate and mask usability of traditional and new N95 respirators when donned by Chinese healthcare workers.

## Research hypothesis

3

We hypothesize that there is no significant group difference in real-time leakage between the use of traditional and new N95 respirators among Chinese healthcare workers during two clinical procedures (i.e., nasopharyngeal suctioning and CPR). We also hypothesize that the fit rate and mask usability have no significant difference between traditional and new N95 respirators among Chinese healthcare workers.

### Trial design

3.1

The study is a randomized controlled, exploratory crossover trial with two arms (*n* = 100 in each arm) to examine and compare the real-time leakage of traditional and new respirators during two standard clinical procedures (i.e., nasopharyngeal suctioning and CPR).

The study will employ two sequential phases. A cross-sectional exploratory design in phase 1 will investigate the fit rate and usability of three types of respirators (two traditional melt-blown respirators with head-loop design and one new nano-respirator with ear-loop and clips) among Chinese HCWs, which is used to identify potential participants for the next phase. A cross-sectional design is appropriate to estimate the prevalence of unfit respirators through testing in a group of large samples.

Phase 2 is a randomized controlled crossover trial with two arms: participants donned with traditional best-fit respirators (either 1860S or 1870+), and participants donned with a new respirator (made of nanomaterial and ear-loop with clip design). A best-fit respirator refers to a given respirator obtaining the highest fit factor when donned by a user. A crossover design has advantages over a parallel experiment because the participating subject will act as his or her control, and possible incomparability between “intervention” and “control groups” could be eliminated. A two-arm study can yield reliable evidence about the effectiveness of real-time protection between traditional and new respirators. Randomization is performed as block randomization with a 1:1 allocation. To protect participants’ rights, anonymity, and confidentiality, the study was designed with the ethical principles of the Declaration of Helsinki. The paper complies with the SPIRIT recommendation for study protocol (25). The overall CONSORT flowchart of the study design is shown in Figure 1.

**Figure 1 fig1:**
[figure not shown]
CONSORT flow diagram.

## Method: participants, interventions and outcomes

4

### Study setting

4.1

This study is being conducted in Hong Kong. Participants will be approached and recruited from web promotion (40% of samples) and invited collaborators (60% of samples), including HCWs (e.g., 20% doctors and 80% nurses based on the ratio of total doctors to nurses in Hong Kong) working in non-governmental organizations and students studying in healthcare disciplines in universities. These organizations provide HCWs who offer treatment and care to patients directly.

### Eligibility criteria

4.2

#### Inclusion criteria

4.2.1

All participants must give written consent for participation following adequate explanation and sufficient understanding before being included in the study.Aged 18 years or above.Healthcare workers who are students or staff (with license) who provide direct care to patients.Certified to perform standard CPR for delivery of basic life support or cardiovascular life support.Have completed an accredited institutional training program and perform CPR in the clinical field.Participants must obtain a pass of fit tests for one traditional N95 respirator (best-fit one) as well as new respirators.

#### Exclusion criteria

4.2.2

Healthcare workers with a history of chronic respiratory diseases or medical conditions (e.g., asthma, congestive heart failure, coronary heart disease, etc.).Pregnant.Having any musculoskeletal diseases that restrict the capacity of CPR performance.

### Who will take informed consent?

4.3

A research assistant will introduce the trial to the participants by demonstration. Participants will also receive an information sheet. The participants are screened with reference to the inclusion criteria, and eligible participants are invited to join the study using a signed written consent with an explanation. The research assistant will then collect the data of fit testing and mask usability results of all three respirators (two traditional respirators and one new respirator), gender, age, and body weight, which are records required for fit testing. Participants who pass one traditional respirator and one new respirator are invited to the phase 2 study.

### Additional consent provisions for collection and use of participant data and biological specimens

4.4

Not applicable.

### Interventions

4.5

#### Explanation for the choice of comparators

4.5.1

To ensure accuracy in comparison of real-time leakage of respirators during CPR, the types of respirators are the infection-control measure serving as an independent variable. Participants receive a traditional best-fit respirator either 3M 1860S or 3M 1870+. All participants are required to don necessary personal protective equipment (assigned N95 respirators, gown, and face shield) for nasopharyngeal suctioning and CPR in the designated simulation environment. Literature indicates that respirator-donning skills, user-seal-check skills, and facial outlook influence the fit-testing results and lead to inaccurate measurement of real-time leakage (3–5). A stringent standardization N95 respirator-wearing protocol is applied (Figure 2), including tying up long hair, standardized psychomotor training on user-seal-check, and standardized psychomotor training on donning skills through video, demonstration, and return demonstration (3–5). Traditional respirators are the commonly used 3 M head-loop respirators in hospitals in Hong Kong, namely the 3 M cup-shaped 1860S and the three-panel-designed 1870+ (7, 8). To the best of our knowledge, these respirators have two of the highest fit rates (3, 5). Participants using these respirators are the control group. New respirators are masks made of nanomaterial and ear-loop with clip design, which have been adopted for clinical use (13). Participants using this new respirator are the intervention group. Comparison of three respirators is presented in Figure 3.

**Figure 2 fig2:**
[figure not shown]
Standardization of N95 respirator-wearing protocol and the flow of crossover trial.

**Figure 3 fig3:**
[figure not shown]
Traditional and new N95 respirators.

#### Intervention description

4.5.2

Eligible participants are randomly allocated in equal proportion to either control or intervention (traditional or new respirator group). New respirator as intervention has been illustrated and described in Figure 3. Standard scenarios are introduced to participants in advance to reduce stress from the environment and psychological factors. Sufficient time is provided for participants to familiarize themselves with the devices and settings. Participants are required to don all necessary personal protective equipment (assigned N95 respirators, gown, and face shield) for nasopharyngeal suctioning and CPR in the designated simulation environment. Data of real-time leakage is recorded at 30 s intervals during the nasopharyngeal suctioning and CPR. After 2 min suctioning (15 s for two times) and a 4 min one-person CPR, participants donned with the tested respirator will perform fit testing and respond to mask usability, which is recorded as data of post-procedure. With a 10 min rest, participants will don another respirator and repeat the measurement of real-time leakage (i.e., crossover), fit test, and usability.

#### Criteria for discontinuing or modifying allocated interventions

4.5.3

Not applicable.

#### Strategies to improve adherence to interventions and scenarios

4.5.4

A face-to-face adherence session will take place at the designated simulated environments. This will include:Instruction to the standardization of N95 respirator-wearing protocol (Figure 2).Importance of following instructions for standard scenarios and measurements of the speed and depth of chest compression to ensure minimal discrepancy.Instruction about the duration of suctioning (i.e., two times suctioning for a maximum of 15 s each) and one-man CPR (a total of 4 min, which included two series of five cycles) (Figure 2).

#### Relevant concomitant care permitted or prohibited during the trial

4.5.5

Not applicable.

#### Provision of post-trial care

4.5.6

Participants enrolled in the study will be monitored by the principal investigator and research nurse continuously to check for problems such as discomfort in performing chest compression, allergic reaction due to the respirators.

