**Figure 4 fig4:**
[figure not shown]
Quantitative fit testing system, tubing connection, and respirator.

Mask usability will be measured by an 11-item Mask Usability Scale (MUS), which involves the wearer’s feedback on tolerated heat, breathability, tightness, interference on speaking, skin itchiness, mask displacement, discomfort on the ear lobe, duration of use, interference on working efficiency, mist over glasses, and overall level of comfort (unpublished data). The MUS is rated on a six-point Likert scale, where a lower score means better usability. We have developed this scale and preliminarily used it in our previous studies (11, 16). We have also validated this scale on 283 nursing students with satisfactory psychometric properties (Cronbach’s alpha = 0.81–0.87; 2-week test–retest reliability: intraclass correlation coefficient = 0.821–0.822).

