### Statistical methods for primary and secondary outcomes

6.1

Statistical Package for the Social Sciences (SPSS) version 27 will be used to perform descriptive and inferential statistical analysis. Descriptive statistics, including mean, standard deviation, percentage, and frequency, will be used to report the demographics, fit rate, and mask usability. The intention-to-treat (ITT) principle will be applied. We expect no carry-over and no period effect for this study based on previous experience. Chi-square test for categorical variables and independent sample t-test for continuous variables will be used to examine comparability among groups by randomization. Independent sample *t*-tests and paired *t*-tests will be used to compare real-time leakage among different groups of tested respirators during procedure, before and after procedures, respectively. Generalized estimating equations (GEE) will be used to evaluate the total real-time leakage difference in the interaction of time and cycles of chest compression. All the tests will be two-sided, and a *p*-value will be set at 0.05 for statistical significance.

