### Composition of the data monitoring committee, its role and reporting structure

7.2

A data monitoring committee (DMC) has been established. The study organizers are not affiliated with the DMC. During recruitment to study, interim analyses will be given to DMC in strict confidentiality. The DMC will provide guidance to the trial steering committee based on the interim evaluations.

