### Adverse event reporting and harms

7.3

Not applicable.

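### Staff watch for allergic reaction and compression discomfort (4.5.6), but harms reporting is declared not applicable (7.3), and no section routes such events to a record by respirator, the monitoring committee or the results

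*Protocol article*

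**What the plan says.** Section 4.5.6 (Provision of post-trial care) commits two roles, the principal investigator and the research nurse, to continuous monitoring of enrolled participants "to check for problems such as discomfort in performing chest compression, allergic reaction due to the respirators".

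Section 7.3, headed "Adverse event reporting and harms", consists only of the answer that the item is not applicable. Section 4.5.3, headed "Criteria for discontinuing or modifying allocated interventions", has the same answer.

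On oversight, section 7.2 says "During recruitment to study, interim analyses will be given to DMC in strict confidentiality" and "The DMC will provide guidance to the trial steering committee based on the interim evaluations". Neither that section nor section 6.2 (Interim analyses) says what the interim analyses contain.

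On tolerability, section 4.6.2 describes an 11-item Mask Usability Scale whose items include "skin itchiness, mask displacement, discomfort on the ear lobe, duration of use, interference on working efficiency". Section 4.5.2 places it after the procedures: "participants donned with the tested respirator will perform fit testing and respond to mask usability, which is recorded as data of post-procedure". It is repeated after the crossover. Section 6.1 says descriptive statistics "will be used to report the demographics, fit rate, and mask usability".

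**The concern.** The protocol foresees that a respirator may cause a reaction and assigns staff to look for one, yet it states that harms reporting does not apply. This cannot be put down to the shortness of an article: the section is present, and its answer sits badly with 4.5.6.

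The matter is not trivial in this design. Each participant performs suctioning and then four minutes of one-person CPR in a tight-fitting respirator, gown and face shield, rests for ten minutes, and repeats the sequence in the other respirator. The respirators differ in material and harness (nanofibre with ear loops and clips against melt-blown with head loops). The Discussion says that better fit, better usability and less leakage would make replacement of all traditional models worth considering. Advice of that reach would normally be read beside a table of adverse events by respirator, and the protocol plans none.

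**Working it through.** The point is textual, so the check is whether any section supplies the route that 7.3 declines to give.

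| Section | What it provides | Route for an observed reaction? |
|---|---|---|
| 4.5.6 | Continuous watching by two roles | Observation only; no record or recipient named |
| 7.3 | Not applicable | No |
| 4.5.3 | Not applicable | No |
| 6.4 (non-adherence, missing data) | Not applicable | No |
| 6.1 | Reports demographics, fit rate, usability; tests leakage | Harms not listed |
| 6.2, 7.2 | Interim analyses go to the monitoring committee | Content unspecified; harms not named |
| 7.4 | Twice-yearly sponsor review of data collection | Events not named |
| 4.6.2 | Mask Usability Scale | Partial, see below |

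**What the usability scale covers.** Its 11 items are heat, breathability, tightness, speaking, skin itchiness, mask displacement, ear-lobe discomfort, duration of use, working efficiency, misting of glasses and overall comfort. Each is a six-point rating given after the procedures. Several bear directly on the contrast between ear loops and head loops. Neither problem named in 4.5.6 (allergic reaction, discomfort in performing compressions) is an item, and no item records that a participant stopped early.

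**What a record could show (illustration only).** The protocol gives no event rate, so there is no figure of its own to reproduce. Inputs: 100 participants in each sequence (section 3.1), 200 in total (section 4.7), each wearing one new and one traditional respirator. If all complete both periods, that is 100 + 100 = 200 wearings per condition. With no events in *m* recorded wearings, the one-sided 95% upper bound on the event rate is 1 − 0.05^(1/*m*).

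- New respirator, *m* = 200: 1 − 0.05^(1/200) = 1.49%.
- Traditional condition, both models pooled, *m* = 200: 1.49%.
- 1860S and 1870+ separately: the 200 traditional wearings are divided by best fit, in a proportion the protocol does not state. If the split were 100/100 (an assumption), each bound would be 1 − 0.05^(1/100) = 2.95%. If it were 50/150, the bounds would be 1 − 0.05^(1/50) = 5.82% and 1 − 0.05^(1/150) = 1.98%.

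These bounds use phase 2 alone. Section 4.5.6 speaks of participants enrolled in the study, so wearings among the 1040 people tested in phase 1 may also fall under its monitoring.

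**The case against.** The best defence is that the two sections do different jobs. Section 4.5.6 sits under post-trial care and is about looking after people; 7.3 is about a formal reporting system. A trial can do the first without the second. The exposure is also modest: about six minutes of simulated work per respirator (2 + 4), on mannequins, by CPR-certified people who have passed fit tests, with chronic respiratory and cardiac disease, pregnancy and limiting musculoskeletal disease excluded. This argues for a light system. It does not explain why harms reporting is inapplicable when respirator-related reactions are expressly watched for.

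Three stronger readings are tempting and are not supported.

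- A reader might infer that harms are seen and then lost. No section says observations go unrecorded. The principal investigator is one of the observers, sits on the steering committee, leads the trial management committee and is responsible for the study reports (7.1.1 to 7.1.3). The interim analyses are not said to exclude safety data. What the text supports is that no route is stated.
- A reader might infer that no harms comparison of any kind exists. The usability scale is collected after each respirator and reported, so self-rated tolerability is compared. The replacement advice in the Discussion is itself conditional on better usability as well as on fit and leakage.
- A reader might apply the 1.49% bound to each respirator model. It holds for the new model and for the two traditional models pooled, but not for 1860S or 1870+ alone.

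**Conclusion.** The concern holds in this limited form. Sections 4.5.6 and 7.3 conflict, and the conflict is explicit. As written, a discrete event such as an allergic reaction, or discomfort during compressions, has no stated path to a record by respirator, to the monitoring committee or to the results. The usability scale narrows the gap without closing it.

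The consequence is confined to safety reporting and to the strength of any advice to replace the traditional models. The primary outcome, sample size, power and type I error are untouched. The 1.49% figure rests on three assumptions (200 completed wearings per condition, every event recorded, none observed). It shows what a record could support and says nothing about how often events occurred. The point should be corrected, but it does not threaten the main comparison.

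**What to change.** Reconcile the two sections. Replace the answer in 7.3 with a statement that every problem found under 4.5.6 is recorded with respirator model and period, passed to the monitoring committee and the ethics committee, and tabulated in the results by respirator: new, 1860S and 1870+, with the number of wearings of each. In a trial still recruiting, this would cost one short form, one table and a little recording time for staff already observing.

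Section 8.1 says the trial is complete and its results are not yet disseminated, so data collection can no longer change. What remains is reporting: tabulate whatever monitoring staff noted, by respirator and period. If no systematic record was kept, say so, and say that any replacement advice rests on self-rated tolerability without a comparison of discrete adverse events. That costs one table or one sentence in the results paper. The change concerns recording and reporting only, and proposes no rule for managing or stopping participants.
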